## Abstract

**Introduction:**

Genito-pelvic pain/penetration disorder (GPPPD) not only adversely affects women’s sexuality and sexual satisfaction but is also associated with a wide range of psychosocial consequences such as reduced quality of life and well-being, mental health comorbidities, and relationship distress. Evidence for effective treatment options is scarce.

**Aim:**

This article describes the rationale, treatment protocol, and study design for a randomized controlled trial examining the efficacy of an Internet-based guided intervention for GPPPD.

**Method:**

Two hundred women who meet the criteria for GPPPD and have not been able to experience sexual intercourse for at least the last 6 months will be recruited and randomly assigned either to the intervention group (IG) or a 6-month waitlist control group. Assessments take place at baseline (T1), peritreatment after completion of Session 5 in IG (T2), after completion of Session 8 or 12 weeks after randomization (T3), and after 6 months (T4). Data will be analyzed on an intention-to-treat and a completer basis.

**Main outcome measures:**

The primary outcome will be sexual intercourse involving the insertion of the partner’s penis at posttreatment. Secondary outcomes include, e.g., improved non-intercourse penetration, sexual functioning, dyadic stress coping, reduced fear of sexuality and negative penetration-related cognitions. Fear of sexuality, penetration-related cognitions, and exercise intensity will be assessed as mediators of intercourse in the IG. Sexual dysfunctions of partners will be measured at baseline (T1) and investigated as a potential moderator of the primary treatment outcome.

**Discussion:**

Given the burden associated with GPPPD and the need for specialized treatment, there is a surprising lack of evidence-based treatment options. This study aims to assess whether Internet-based interventions could contribute to closing this treatment gap.

**Clinical Trial Registration:**

German Register of Clinical Studies (DRKS): DRKS00010228.

## Background

Genito-pelvic pain/penetration disorder (GPPPD) is a new diagnosis included in the 5th edition of the Diagnostic and Statistical Manual of Mental Disorders (DSM-5), which merged the revised definitions of both female sexual dysfunctions dyspareunia and vaginismus (1). At least one of the following persistent or recurrent criteria characterizes GPPPD: (1) difficulties with vaginal penetration during intercourse, (2) genito-pelvic pain during vaginal intercourse or penetration attempts, (3) fear or anxiety associated with genito-pelvic pain or vaginal penetration, or (4) tightness of the pelvic floor muscles during attempted vaginal penetration (1). One or more of these symptoms have to be present for at least 6 months and must cause clinically significant distress. GPPPD can be classified as either lifelong or acquired and, depending on the level of distress as mild, moderate or severe (1). The fusion of vaginismus and dyspareunia under a new classification and set of criteria was due to the significant overlap in clinical presentation, and exceeding difficulties to distinguish between the two reliably (2, 3).

The prevalence of GPPPD has not been ascertained due to the novel criteria set. Reported prevalence rates in the general population vary between 3 and 25% for dyspareunia (4–8) and 0.4 and 6.6% for vaginismus (6, 7, 9). Prevalence estimates are heterogeneous due to, e.g., varying diagnostic criteria, assessment methods, study design, and sample characteristics (10–12).

The burden of suffering associated with GPPPD and linked conditions such as vulvodynia and provoked vestibulodynia is high as symptoms have a detrimental impact on physiological and psychological health, and relational well-being. GPPPD has been shown to have a negative effect on the women’s overall quality of life (13), with 60% of women reporting that the disorder compromised their ability to enjoy life (14). Moreover, it has been linked to depression and anxiety disorder (15–17). GPPPD symptoms are often comorbid with a wide range of other sexual dysfunctions and reduced sexual behavior (18–20). Many women with GPPPD also experience problems when using tampons or during gynecological examinations (21, 22). GPPPD has been shown to contribute to declines in self-esteem and feelings of femininity and is associated with a negative body and genital self-image (23–25). It can pose a considerable burden on a couples’ relationship, especially if they would like to have children (26).

Regarding the broad symptom profile of GPPPD, its etiology and maintenance can be best explained by a biopsychosocial framework considering a wide range of interdependent pathophysiological, psychological, social, cultural, and relational factors as well as critical life events (27). According to the fear-avoidance model (28), maladaptive cognitions including worrying about losing control of one’s body, genital incompatibility, and pain catastrophizing are crucial in maintaining and reinforcing genito-pelvic pain and associated GPPPD symptoms, by leading to fear and hypervigilance in sexual situations, or complete avoidance of sexual intimacy (18, 29, 30). Beyond individual aspects, relationship dynamics such as dyadic communication and stress coping, as well as partners’ responses have been shown to have profound influence on GPPPD symptoms (31–33). To an appreciable extent, GPPPD has also been found to concur with male partners’ sexual dysfunctions (34, 35).

Due to the biopsychosocial nature of GPPPD, a multidimensional integrative treatment approach is needed that targets not only difficulties with vaginal penetration, pain, anxiety, and muscle tightness associated with sexual intercourse but also sexual satisfaction and couple dynamics (36–38). Psychological interventions for vaginismus and dyspareunia include strategies such as pain management, systematic desensitization, cognitive restructuring, pelvic-floor exercises, sensate focus, and mindfulness (39–41). Only few interventions, however, have been empirically tested so far. Of these trials, only few studies have applied randomized controlled trial (RCT) design, most of them with only small sample sizes (42–45). Findings of these RCTs indicate that psychological treatments can result in significant improvement of intercourse penetration ability, decrease in pain during intercourse, and higher levels of sexual functioning (42–45). However, none of these studies targeted all symptoms of GPPPD.

Moreover, the availability of such specialized treatment options in health care is extremely limited (46, 47). Thus, the majority of women with GPPPD do not receive appropriate treatment, which is, alongside the burden for the individual and partner, also associated with economic consequences, such as increased direct health costs including office visits, hospitalization, and medication (48). Many women with GPPPD do, however, not seek help in the first place although feeling severely distressed (49). Reasons therefore include (1) sexual dysfunctions not being regarded as recognized disorders, and instead a taboo subject in society associated with fear of stigmatization (50, 51), (2) self-stigmatization including feelings of shame and guilt (25, 50, 52), (3) health care professionals not standardly inquiring about sexual difficulties in routine care visits due to feelings of inadequacy or embarrassment or due to a lack of training, knowledge, or time (53, 54).

Internet-based interventions can be one strategy to address some of the limitations of traditional psychological interventions with regard to limited availability, high threshold, and costs (55). They (1) are readily available and easily accessible independent of time and place, (2) offer anonymity, (3) allow users to work at their own pace and to review materials as often as they want, (4) are more likely to reach affected women earlier compared with traditional mental health services, hence preventing the onset of other mental health problems, (5) reach women who might otherwise not seek out help (56), and (6) are easily scalable regarding implementation and dissemination. In both community and clinical settings, Internet-based interventions have been shown to be an effective mean to treat other sexual dysfunctions (57–60), anxiety (61, 62) and depression (63–65) amongst other mental health disorders (56). However, to the best of our knowledge, there is no published trial evaluating an Internet-based guided intervention for GPPPD in an RCT design.

### Aims

In this study, we will investigate the efficacy of a newly developed Internet-based guided self-help intervention for GPPPD. We hypothesize that participants in the intervention group (IG) are more likely to achieve intercourse penetration, the primary outcome in this study, from pretest to posttest, compared to a waitlist control group (WCG), and that this effect will also be sustained until a 6-month follow-up. In addition, the study aims (1) to analyze changes concerning secondary outcomes compared to the WCG, (2) to assess predictors and moderators of intercourse penetration and treatment adherence in explorative analyses, (3) to analyze fear of sexuality, penetration-related cognitions, and exercise intensity as mediators of intercourse penetration in the IG, (4) to investigate sexual dysfunctions of partners as a potential moderator of treatment outcome, and (5) to examine patients experiences with the intervention and treatment adherence qualitatively in order to further improve Internet-based interventions for GPPPD.

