## Methods

### Design

An RCT will be conducted to compare the IG (Paivina-Care) with a WCG. Self-reported assessments will take place at baseline (T1), peritreatment (after completion of Session 5, T2 in IG), posttreatment (after completion of Session 8 or 12 weeks after randomization, T3) and at a 6-month follow-up (T4; see Figure 1 for a detailed overview). Self-reported data will be collected using a secure online-based assessment system (AES, 256-bit encrypted). All procedures involved in the study will be consistent with the generally accepted standards of ethical practice. The study was approved by the Friedrich-Alexander University Erlangen-Nürnberg ethics committee (no. 324_15B). The trial is registered in the German clinical trials register under DRKS00010228. All participants gave written informed consent in accordance with the Declaration of Helsinki.

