### Primary and Secondary Outcomes

Primary outcome will be sexual intercourse at posttreatment. In secondary analyses, the effects of the intervention, e.g., on nonintercourse penetration behavior, fear of sexuality, sexual functioning, and cognitions regarding vaginal penetration, will be examined.

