### Outcome Measures

#### Intercourse Penetration

The seven-item PEQ will be used as a primary outcome measure. Successful intercourse penetration (SIP) will be measured by one item assessing the degree to which the insertion of the partner’s penis was possible. The items will be answered on a 4-point Likert scale (0 = not attempted; 1 = attempted, but unsuccessful; 2 = attempted and sometimes successful; 3 = attempted and always successful). Previous cases of women reaching SIP prior to treatment completion have shown that they are susceptible to study dropout (67). For that reason, participants who do not fill out the PEQ online, (1) are scheduled for a telephone assessment or (2) can report to their eCoach whether intercourse penetration was successful.

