#### Nonintercourse Penetration

Successful nonintercourse penetration will be measured by the remaining six items of the seven-item PEQ. These items assess the degree to which insertion of one or two fingers or another object such as a tampon or a dilator by the woman or her partner was possible. Participants will be asked to answer questions referring to the past two weeks. Cronbach alpha was found to be good (α = 0.81) for this scale (67).

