### Sample Size Calculation

We aim to include 200 participants to statistically detect a minimal clinical relevant effect size of *w* = 0.20, with a power (1 − β) of 80% and an alpha of 0.05 (two-tailed test) for an intention-to-treat analysis using G*Power. The design of the study is based on the expected superiority of the IG compared to the WCG on the primary outcome variable (i.e., sexual intercourse) at posttreatment (T3).

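### The fallback route for the primary outcome (an undated, unscaled report to the eCoach) is not tied to T3, so an early success can be entered as the posttreatment value, probably mainly in the intervention arm

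*Protocol article*

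**What the plan says.** The time point is given consistently. The abstract states: "The primary outcome will be sexual intercourse involving the insertion of the partner’s penis at posttreatment". The section Primary and Secondary Outcomes repeats it: "Primary outcome will be sexual intercourse at posttreatment". The Sample Size Calculation also refers to T3. The Design section places T3 after Session 8 or at 12 weeks after randomization. The Aims section words the hypothesis a little differently, as women being "more likely to achieve intercourse penetration, the primary outcome in this study, from pretest to posttest".

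The section Intercourse Penetration measures the outcome with one PEQ item scored 0 to 3, which the inclusion criteria call item 7. It gives no recall period for that item. It then explains why a fallback is needed: "Previous cases of women reaching SIP prior to treatment completion have shown that they are susceptible to study dropout". Women who do not fill out the PEQ online are scheduled for a telephone assessment, or they "can report to their eCoach whether intercourse penetration was successful".

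The only recall period in the article is in the next section, Nonintercourse Penetration, which covers the other six items: "Participants will be asked to answer questions referring to the past two weeks".

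The section on eligibility and randomization gives the waitlist control group (WCG) access to the program 6 months after study intake. The Support section describes the eCoach as part of the intervention.

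**The concern.** The fallback is aimed at women whose success came before the end of treatment and who then stopped responding. The eCoach report asks whether success occurred. It does not ask when, and it does not use the 0–3 item. Nothing in the text prevents that earlier success from becoming the T3 value.

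Take two women in the intervention group (IG) who both succeed in week 6 and not in the weeks before T3. One leaves and tells her eCoach about the success. The other stays and answers the T3 questionnaire. If the item covers a recent period, the first is scored a success and the second scores 0 or 1.

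The primary chi-square test would then compare a blend of current status and past success, and the blend could differ by arm. WCG women have no program before month 6 and therefore, it appears, no eCoach contact during the primary period. Any such error would raise the IG rate.

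**Working it through.** **1. The plan's own figure.** N = 200 and w = 0.20 give λ = N·w² = 200 × 0.04 = 8. With 1 df and two-sided α = 0.05, power is 0.807; 80% power needs N = 197. The stated 200 reproduces and is not in dispute.

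**2. One history through three routes** (success in week 6, not maintained):
- Online PEQ at T3: scored 0–3, window not stated. The result is 0 or 1 if the window is recent, but can be 2 (sometimes successful) if the window reaches back to week 6.
- Telephone assessment: wording and window not stated. It gives the same result as online if the same item is asked.
- eCoach report: no date, window or scale. It counts as a success.

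The routes disagree only if the item's window is short. Applying the two-week window to the intercourse item is an assumption.

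**3. Illustrative size.** The documents give no rates, so every input here is assumed, including 100 women per arm. Let E be the share who ever succeed by T3. Let k be the share of those also successful in the T3 window. Let d be the share of ever-successful women scored from an earlier report.
- Status at T3: E·k.
- Mixture of routes: E·[d + (1 − d)·k].
- Excess over status: E·d·(1 − k).

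No true difference, E = 0.30 in both arms, fallback used in the IG only:
- Central (k = 0.7, d = 0.3): excess 0.30 × 0.3 × 0.3 = 0.027, so 0.237 against 0.210. w = 0.0135/√(0.2235 × 0.7765) = 0.032; λ = 0.21; rejection rate 7.4% instead of 5%.
- Low (k = 0.9, d = 0.1): excess 0.30 × 0.1 × 0.1 = 0.003; rejection rate about 5%.
- High (k = 0.5, d = 0.5): excess 0.30 × 0.5 × 0.5 = 0.075, so 0.225 against 0.150. w = 0.096; λ = 1.85; rejection rate 27%.
- Same d in both arms: 0.237 against 0.237, so no distortion.
- k = 1 (success always maintained, or a window long enough to catch it): no distortion.

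True difference, E = 0.30 (IG) and 0.15 (WCG), k = 0.7:
- By status: 0.210 − 0.105 = 10.5 points.
- By ever achieved: 15.0 points.
- Mixture, fallback in the IG only (d = 0.3): 0.237 − 0.105 = 13.2 points.
- Mixture, d = 0.3 in both arms: 0.237 − 0.15 × 0.79 = 0.237 − 0.1185 = 11.85 points.

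Equal use of the fallback therefore removes the false positive under equal arms. When the arms differ, the estimate still lies between the two definitions.

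**The case against.** A reader might infer that the article contains three conflicting definitions of the primary outcome. It does not. The abstract, the outcome section and the sample size section agree on posttreatment. Every woman enters with a score of 0 or 1 on item 7, so the Aims wording reads naturally as moving from inability at pretest to success at posttest. The same sentence expects the effect to be sustained to 6 months, which suits a status at a time point. The wording is loose but does not contradict the other sections.

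A reader might also take early success to be the scoring rule. The article gives it only as the reason why some women will not fill out the questionnaire. The telephone route is not limited to one arm and can be read as the same item asked another way. A woman who leaves treatment also still has a T3 at 12 weeks.

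The example depends on a short window for item 7. The inclusion criteria point the other way, because they use that item to indicate inability over at least 6 months. With a long window the two women could both count as successes. The calculation also places the fallback in the IG alone and uses invented rates.

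Finally, a condensed article may leave question wording to the full protocol. This carries some weight for the recall window alone. It does not cover the fallback rule, because the article itself states that rule and lets an undated, unscaled report supply the primary outcome. A later analysis plan cannot recover a date that was never asked.

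**Conclusion.** The point holds in a limited form. The outcome is defined at T3, but the eCoach report that may replace it has no date, window or 0–3 score, and it is meant for women expected to have succeeded earlier. An unmaintained early success can therefore be scored differently by route.

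The direction, towards the IG, rests on the inference that WCG women have little or no eCoach contact in the primary period. The disagreement between routes rests on item 7 having a recent window. The documents do not settle either assumption.

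The size cannot be derived from them. Under the assumed inputs the distortion is modest in the central case (2.7 points, 7.4% rejection). It becomes serious only when k and d are both at their extremes (7.5 points, 27%), and it vanishes under equal arms if the fallback is used equally. The sample size is unaffected. The change is worth making because it is cheap and settles what the primary result means.

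**What to change.** - State one reference window, ending on the T3 date, for PEQ item 7. Ask the same item in the same words online and by telephone, in both arms.
- Do not enter an earlier or undated eCoach report as the T3 value. Record it with its date and use it as a predictor when a missing T3 value is imputed.
- Analyse ever achieved since randomization as a secondary or sensitivity outcome, collected with the same questions in both arms.
- Reword the hypothesis in Aims so that it refers to penetration at posttest.

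The cost is some wording and one date item. A few early successes would no longer count automatically, so the IG rate may be slightly lower. A few more T3 values would need a call or imputation, among the women the article already expects to lose. The dated reports used in the imputation, and the separate ever-achieved analysis, keep that information in use.

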**Other measurements**					
Socio-Demographic Questionnaire	✓	–	–	–	–
Childhood Trauma Questionnaire	–	✓	–	–	–
Dyadic Coping Inventory	–	✓	–	✓	✓
Partnership Questionnaire Short Form	–	✓	–	✓	✓
State Trait Anxiety Inventory	–	✓	–	✓	✓
Generalized Anxiety Disorder 7-Item Scale	–	✓	–	✓	✓
Well-Being Index	–	✓	–	✓	✓
Self-Esteem Scale	–	✓	–	–	–
Health Action Process Approach Questionnaire	–	✓	✓	–	–
Client Satisfaction Questionnaire	–	–	–	✓	–
Inventory for the Assessment of Negative Effects in Psychotherapy	–	–	–	✓	✓
Regular practicing of the exercises	–	–	–	✓	✓
Potential dropout reasons	–	–	–	✓	✓
Utilization of additional help	–	–	–	✓	✓

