**Questionnaires for the partner**					
Socio-Demographic Questionnaire	–	✓	–	–	–
International Index of Erectile Function for Men	–	✓	–	–	–

*T0 = screening, T1 = baseline, T2 = after Session 5 assessed in IG, T3 = posttreatment, T4 = 6-month follow-up*.

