#### Predictor, Moderator, and Mediator Analyses

Predictors and moderators of changes in SIP will be analyzed on an exploratory basis. They will include, e.g., lifelong and acquired GPPPD, experiences of sexual abuse, and symptom severity. Fear of sexuality, penetration-related cognitions and exercise intensity will be examined as mediators of changes in SIP *via* structural equation modeling. Separate moderator analyses will be conducted using the PROCESS macro for SPSS. The analyses will include the main effect of the baseline variable, the main effect of the treatment condition (IG and WCG), and the interaction of the baseline variable and the treatment condition. To assess relevant subgroup effects, follow-up simple slope analyses for possible significant interaction effects will be conducted. Therefore, the slope and the significance of the intervention main effect will be evaluated for conditional values (one SD below and one SD above the mean) of the moderator.

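### Mediation is confined to the intervention group, so it can show within-arm associations but not mediation of the treatment effect

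*Protocol article*

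**What the plan says.** The restriction to the IG appears twice. The Aims set out "to analyze fear of sexuality, penetration-related cognitions, and exercise intensity as mediators of intercourse penetration in the IG", and the Abstract repeats that "exercise intensity will be assessed as mediators of intercourse in the IG". The section on predictor, moderator and mediator analyses says that these variables "will be examined as mediators of changes in SIP" (SIP is successful intercourse penetration), by structural equation modelling. It neither repeats nor lifts the restriction, and it names no time point for mediator or outcome. The same section does put treatment condition, with both arms, into the moderator models.

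On timing, the Design section defines the second assessment as "peritreatment (after completion of Session 5, T2 in IG" and the third as "posttreatment (after completion of Session 8 or 12 weeks after randomization, T3". The Table 2 footnote confirms "T2 = after Session 5 assessed in IG". The Table 2 row "Regular practicing of the exercises" is ticked at T3 and T4 only. The primary outcome is intercourse at posttreatment, which is T3.

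**The concern.** Mediation of a treatment effect means that allocation changes the mediator and the mediator in turn changes the outcome. If only treated women are analysed, the first link cannot be estimated. What remains is an association between fear, cognitions or practice and intercourse among treated women. Randomisation does not protect that association from confounding.

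Two features of the schedule add to this. A T2 value depends on finishing Session 5, an event after randomisation that may be related to both mediator and outcome. Exercise intensity is first recorded at the same assessment as the primary outcome, so women who have succeeded may report less practice because they succeeded.

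Mediation is a named aim, and the Strengths section presents it as a gain of the trial. Reported as planned, associations within one arm could be read as the mechanism by which the programme works.

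**Working it through.** **1. The plan's own figure.** The only stated sample size is for the primary chi-square test (w = 0.20, two-sided alpha 0.05, power 80%). N = (1.960 + 0.842)² / 0.20² = 196.2, rounded up to 197. At N = 200 the power is 0.807. The stated 200 is sound for its own test. The article gives no sample size or power for the mediation aim.

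**2. The schedule from Table 2.**

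| Measure | T1 | T2 (IG, after Session 5) | T3 | T4 |
|---|---|---|---|---|
| Fear of Sexuality Questionnaire (FSQ) | yes | yes | yes | yes |
| Vaginal Penetration Cognition Questionnaire (VPCQ) | yes | yes | yes | yes |
| Primary Endpoint Questionnaire (PEQ) | yes | yes | yes | yes |
| Exercise item | no | no | yes | yes |

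Only T2 is limited to one arm. Three things follow.
- For fear and cognitions, change from T1 to T2 precedes T3, but only among Session 5 completers. PEQ is also asked at T2, so some women may already have succeeded by then.
- For fear and cognitions, T3 precedes T4 and is scheduled in both arms. The waitlist control group (WCG) gets access 6 months after intake, and T4 is the 6-month assessment, so T4 is planned while the WCG is still untreated.
- For exercise, T3 precedes T4, but nothing is scheduled before T3.

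**3. Who has a T2 value.** T3 has a 12-week calendar fallback and T2 has none. The Intercourse Penetration section says that women who succeed early are prone to drop out. The Discussion reports marked non-adherence in a pilot at the sessions with insertion exercises, and here finger insertion begins in Session 3. Absence of T2 may therefore depend on both outcome and mediator.

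Illustration, assuming 1:1 allocation (ratio not stated), so 100 IG women, and an assumed share who finish Session 5. The smallest correlation detectable with 80% power is r = tanh[(1.960 + 0.842) / √(m − 3)].
- m = 100: tanh(2.802 / √97) = 0.28
- m = 90: tanh(2.802 / √87) = 0.29
- m = 50: tanh(2.802 / √47) = 0.39

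Power to detect an association of 0.20 is 0.52, 0.48 and 0.29 respectively.

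The bias from this selection is unknown. In a simulation under assumed relations, with Session 5 completion depending on fear and motivation, the fear–outcome correlation moved from −0.22 to −0.19. With early-success dropout added, it moved from −0.22 to −0.21.

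**4. Exercise and outcome both at T3.** Simulation with 100 women, an assumed 35% success rate and no effect of exercise on intercourse. If success itself lowers reported practice by 0.3, 0.5 or 0.8 SD, a significant association appears in about 29%, 65% or 97% of trials, against about 5% with no shift. The shifts are assumptions; they show only that the concurrent association cannot be read in one direction.

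**The case against.** Read literally, Aim 3 is a process question inside one arm, and nowhere does the article promise the share of the arm effect that is mediated. The mediator section fixes no time points, and detail of that kind may stand in a fuller document. Multiple imputation is planned for missing data. The Adherence Measures section asks about practice in a given week without saying when, and the Intervention section describes a daily online diary.

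Much of this stands, and it rules out stronger readings that a reader might infer.
- *That the aim cannot be answered at all.* Not supported: T1-to-T2 change in fear and cognitions precedes T3, and the schedule also allows a two-arm analysis of both.
- *That non-adherent women have no mediator value.* True only of T2; the T3 fallback still schedules them for FSQ and VPCQ.
- *That exercise never precedes the outcome.* True only for intercourse at T3; T3 practice precedes T4 intercourse.
- *That a known fraction of the IG is lost at T2.* The article gives no completion rate.

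The rest does not remove the point. The IG-only restriction is a stated choice, not an omitted detail. Imputation does not create an arm contrast, and for a woman who never finishes Session 5 the T2 assessment is not merely missing but undefined. The diary is optional, and it is not named as the measure of exercise intensity.

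**Conclusion.** The concern holds in a limited form. As stated, the analysis can yield only associations within the IG. Any use of T2 mediators is confined to women who finished Session 5. For exercise intensity, no scheduled measurement precedes the T3 outcome. None of this should be reported as mediation of the treatment effect.

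The main fault for fear and cognitions is the restriction to one arm, not the data collected. Exercise intensity is the weakest of the three, because it has no natural counterpart in the WCG. The size of any bias cannot be derived from the article; the figures above rest on assumed allocation, completion, success rate and reverse effect. The aim is secondary, so the plan should be corrected, but the primary test and its sample size stand.

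**What to change.** - **Fear and cognitions:** lift the IG-only restriction. Fit a two-arm model with arm, FSQ or VPCQ at T3 (adjusted for its T1 value) and SIP at T4, with T4 completed before the WCG gets access. State the assumption of no unmeasured confounding between mediator and outcome, which randomisation does not secure.
- **T3 PEQ:** adjust for it only in a sensitivity analysis. It contains the primary outcome and may lie on the causal path, so adjusting for it in the main model would change the question to additional change after T3.
- **T2 analysis:** label it an IG process analysis among Session 5 completers.
- **Exercise intensity:** treat it as an IG-only predictor. Add the existing one-item question to the T2 form for women who have not yet reached T2. Relate T2 exercise to T3 SIP, and T3 exercise to T4 SIP.

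The cost is revised wording and one extra item on an online form. The Current Status section shows recruitment still open, so the item could reach later participants; women already past T2 would lack it. The two-arm mediation outcome would be taken at T4, where more data may be missing than at T3.
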